### Trial treatments

#### Randomisation procedures

Randomisation in each part of the factorial will be stratified by centre and the other randomisations in the factorial. Randomisation lists, using variable block sizes, will be generated and kept at the Medical Research Council Clinical Trials Unit (MRC CTU), London. The randomisation envelopes and clinical packs will be prepared before the trial, with 1 set for complicated SA (R1a) and 1 for uncomplicated SA (R1b). Eligible children will be screened and recruited at the time of hospital admission. At enrolment sealed consecutively numbered opaque envelopes (opened in strict numeric order) will assign a TRACT trial number and indicate a clinical pack number. The clinical pack will be within the first 10 packs in the study filing cabinet but will not necessarily be the first remaining clinical pack number (an additional level of allocation concealment). Once opened, the clinical pack contains case report forms (CRFs) and a card which confirms the TRACT trial number, and simultaneously assigns transfusion interventions R1a/b (according to SA strata), micronutrient support (R2) and antimicrobial prophylaxis (R3) randomly. A similar system has worked well in the emergency care trial, FEAST [16].

The randomisation procedures and adherence to allocated treatments are reviewed at each independent monitoring visit. The process for this is detailed within the monitoring Standard Operating Procedure (SOP). The monitors are requested to check at each participating site whether: a) the randomisation envelopes are being correctly stored and used; b) whether enrolled children are allocated to the correct arm and c) that the allocated trial treatments (transfusion, MVMM/iron or folate and cotrimoxazole) were received by the child. It is also monitored electronically through central database monitoring, and also that both the Data Monitoring Committee (DMC) and the Trial Steering Committee (TSC) will monitor overall adherence to each of the randomised allocations.

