#### R1a complicated severe anaemia

Children fulfilling these severity criteria will be randomly allocated on a 1:1 basis to receive one of the following:○ Whole blood transfusion 20 ml/kg, alternatively 10 ml/kg packed cells; or○ Whole blood transfusion 30 ml/kg, alternatively 15 ml/kg packed cells

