#### R1b uncomplicated severe anaemia

Children with an Hb 4–6 g/dl without any severity features will be randomly allocated on a 1:1:2 basis to receive one of the following:○ Whole blood transfusion 20 ml/kg alternatively 10 ml/kg packed cells, or○ Whole blood transfusion 30 ml/kg alternatively 15 ml/kg packed cells, or○ No transfusion (control, SOC)

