### Transfusion treatment schedule

A clinician or medical officer will prescribe the blood, using a calculator, to determine the volume of whole blood required (20 or 30 ml/kg). If only packed cells are available then the clinician must re-calculate the equivalent volumes of packed cells (10 or 15 ml/kg). Transfusions will be administered in gauged blood burettes; an initial aliquot (2 ml) will run into a sterile apex tube using an aseptic technique (and ensuring that the tip of the infusion set does not touch anything, to prevent contamination) and 1 drop taken from this to record the Hb and haematocrit of the donor blood. Whole blood will be run over 3–4 hours and packed cells can be administered over 2–3 hours.

For all children in the trial an additional, or initial (for SOC control group in R1b only), transfusion(s) will be permitted after 8 hours (at the point of the first reassessment of Hb) for children who still have either: (i) profound anaemia Hb < 4 g/dl, irrespective of other signs of severity; (ii) SA 4–6 g/dl and one or both de novo signs of severity (respiratory distress or impaired consciousness); (iii) uncorrected SA 4–6 g/dl in children with an acute history of haemoglobinuria or known sickle cell disease. Early sampling of Hb (<8 hours from baseline), and additional transfusion, will be permitted in children randomised to any group in the R1b strata (uncomplicated SA) developing de novo signs of severity.

If a child randomised to no-transfusion control (R1b only) meets the above criteria, they will receive 20 ml/kg whole blood or 10 ml/kg packed cells, as recommended by the WHO [3]. Children randomised to initially receive blood (R1a and R1b) who subsequently meet the above criteria will follow their randomisation arm: that is they will receive either an additional transfusion of 20 ml/kg or 30 ml/kg of whole blood (or 10 ml/kg or 15 ml/kg packed cells respectively). Any child who has already received 2 transfusions and subsequently fulfils the criteria above will receive a maximum of 20 ml/kg (or 10 ml/kg packed cells) irrespective of randomisation. Frusemide or other diuretics will be prescribed at the discretion of the attending physician and not used routinely in the trial.

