### Statistical analysis

The analyses will be described in detail in a full Statistical Analysis Plan. In brief, each intervention is hypothesised to be superior to SOC and, therefore, the proposed analysis is intention-to-treat, including all randomised patients. The primary analysis will compare: a) transfusion versus no transfusion (strata b only) and b) 20 ml/kg versus 30 ml/kg (strata a and b) in terms of the proportion of children with fatal outcome 28 days after randomisation. Primary outcome analysis will use time-to-event methods (Kaplan-Meier, log-rank test, proportional hazards models) to the timepoints specified for primary and secondary outcomes, stratified by centre and anaemia severity at baseline. Correction of anaemia will also be analysed using time-to-event methods.

Pre-specified subgroup analyses will include each of the other randomised allocations (ie exploration of interactions in the factorial design), together with the other randomisation stratification factor (centre) and the anaemia stratification factor (a versus b) for the transfusion randomisation. We will also investigate a priori whether there was any evidence for a different impact of the interventions according to the following categorical variables: previous receipt of a transfusion (ever or at another health centre in this illness); speed (rate) at which the transfusion is administered; fever; malaria; microbiological evidence of sepsis (blood culture or retrospective molecular diagnosis); HIV; known or previously undiagnosed sickle cell disease.

For the cotrimoxazole prophylaxis and MVMM supplementation randomisations the primary analysis will be intention-to-treat based on all randomised participants, as above. However, secondary analyses will be restricted to: (i) patients discharged alive, and (ii) patients discharged alive in whom these interventions were neither mandated nor contraindicated (ie excluding HIV-infected children and those with known GP6D deficiency from the cotrimoxazole randomisation, and excluding children admitted for severe acute malnutrition from the supplementation randomisation).

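### For the transfusion comparisons (R1), speed of transfusion arises after randomisation and should not be listed as an a priori effect modifier

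*Protocol article*

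**What the plan says.** The Statistical analysis section introduces a list of subgroup variables with "We will also investigate a priori whether there was any evidence for a different impact of the interventions according to the following categorical variables". The list includes "speed (rate) at which the transfusion is administered", alongside patient characteristics such as fever, malaria, HIV and sickle cell disease. Nothing there limits the item to transfused children, to one of the randomisations, or to an observational reading.

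Three other parts of the article bear on it:

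- **Timing of allocation** (Randomisation procedures): the card in the clinical pack opened at enrolment "simultaneously assigns transfusion interventions R1a/b (according to SA strata), micronutrient support (R2) and antimicrobial prophylaxis (R3) randomly".
- **Volumes and infusion time** (R1a complicated severe anaemia; Transfusion treatment schedule): the arms are "Whole blood transfusion 20 ml/kg, alternatively 10 ml/kg packed cells" and "Whole blood transfusion 30 ml/kg, alternatively 15 ml/kg packed cells". The time allowed depends on the product and not on the volume: "Whole blood will be run over 3–4 hours and packed cells can be administered over 2–3 hours".
- **Control arm** (R1b uncomplicated severe anaemia; Transfusion treatment schedule): allocation is 1:1:2, with the double share going to no transfusion. On meeting clinical criteria, "an additional, or initial (for SOC control group in R1b only), transfusion(s) will be permitted after 8 hours".

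**The concern.** A subgroup analysis asks whether a randomised effect differs between kinds of patient who could have been told apart before allocation. If the subgrouping variable comes after allocation and is affected by it, the arms within a subgroup are no longer comparable, and the interaction test no longer estimates a difference in treatment effect.

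Transfusion speed fits that description for R1. A larger volume run over the same time must run faster, so the slow and fast groups can consist mainly of one arm each. In the no-transfusion arm of R1b there is no initial transfusion whose speed could be classified.

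The safety of the larger volume is one of the concerns that the Discussion sets out to answer. A statement that 30 ml/kg does worse when given fast could be an artefact of how the groups were formed, yet it would be reported with the standing of a pre-specified result.

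**Working it through.** **1. The comparison that would be split.** The article's figure for 30 versus 20 ml/kg is 2798 children, 1399 per group (13.67 % versus 9.57 %, two-sided alpha 0.013, power 80 %). The two-proportion formula gives n = 1350 per group without continuity correction. With it, n′ = (n/4) × [1 + √(1 + 4/(n·d))]² and d = 0.1367 − 0.0957 = 0.041. So n′ = 337.5 × [1 + √(1 + 4/55.35)]² = 337.5 × 4.143 ≈ 1398.4, rounded up to 1399. The stated figure reproduces and is not in question.

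**2. Order of events.** R1 is assigned when the pack is opened at enrolment. The trial transfusion follows, so its speed is known only after allocation. No definition or cut-point changes that.

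**3. Rates implied by the article's own volumes and times.** Rate = volume ÷ duration, in ml/kg/h:

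| Product | Conservative arm | Liberal arm |
|---|---|---|
| Whole blood, 3–4 h | 20/4 = 5.0 to 20/3 = 6.7 | 30/4 = 7.5 to 30/3 = 10.0 |
| Packed cells, 2–3 h | 10/3 = 3.3 to 10/2 = 5.0 | 15/3 = 5.0 to 15/2 = 7.5 |

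At nominal volumes the whole-blood ranges do not overlap, and the packed-cell ranges meet only at 5.0.

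**4. What a median split on ml/kg/h would do.** The share of packed cells and the spread of durations are not given. I assumed durations uniform within the stated window and varied the packed-cell share in a simulation of 400,000 children, pooling products without conversion:

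| Packed-cell share | 30 ml/kg arm in fast half | 20 ml/kg arm in fast half |
|---|---|---|
| 0 % or 100 % | about 100 % | about 0 % |
| 10 % | 93 % | 7 % |
| 25 % | 85 % | 15 % |
| 50 % | 79 % | 21 % |
| 75 % | 82.5 % | 17.5 % |

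The probability that a child from the 30 ml/kg arm has a higher rate than one from the 20 ml/kg arm (AUC) is 0.91 to 1.00 throughout. On 1399 per group, the 50 % row puts about 0.787 × 1399 = 1101 children of one arm and 0.214 × 1399 = 299 of the other in the fast half. Product mix then differs by arm too: at that share the median lies above 5.0, which 10 ml/kg of packed cells cannot exceed. The fast children in the conservative arm would therefore all have had whole blood, while those in the liberal arm would have had either product.

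**5. Deviation from nominal volume.** The Discussion counts pilot delivery within 5 ml/kg as following allocation (98 % and 96 % of the two arms). At that limit, whole blood could run at up to 25/3 = 8.3 ml/kg/h in the 20 ml/kg arm and as low as 25/4 = 6.25 in the 30 ml/kg arm. Overlap is therefore possible at the extremes.

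**6. Speed as hours.** If speed means duration, the stated windows do not link it to volume, and the same simulation splits each arm about 50/50. Step 2 still applies.

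**7. R1b.** Under 1:1:2, the no-transfusion share is 2/4, one half. On the planned 466 × 4 = 1864 uncomplicated cases, that is 932 children without an initial rate. Those transfused later qualify by criteria met after randomisation. An interaction needs the effect of transfusion versus none at each speed, and the control arm cannot be sorted by speed, so it cannot be estimated.

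**The case against.** The strongest reply is that the article only names the variable and leaves detail to a full Statistical Analysis Plan. That plan could define speed by hours, or as faster or slower than the stated window, and the link to volume would then largely disappear. This stands as a limit on the rate figures, which are conditional on ml/kg/h within a product at nominal volumes. It does not answer the main point: under any definition speed follows allocation in an open-label trial, and it has no value at baseline in the no-transfusion arm.

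A second reply is that this is one entry in a list of secondary explorations, and that the 20 versus 30 ml/kg comparison excludes the no-transfusion arm by design. Both are true. Missing rates in R1b affect only transfusion versus no transfusion.

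A reader might also infer more than the documents support:

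- **That speed simply is the arm.** Pooled products and volume deviations allow overlap, so volume dominates without being the sole determinant.
- **That half of R1b can never have a rate.** Some controls are transfused later. They have a rate, but they are a selected group.
- **That deteriorating children are transfused at a different rate.** The treatment schedule provides for earlier haemoglobin sampling and additional transfusion on deterioration. It does not mention a changed rate.
- **That R2 and R3 are affected.** Those treatments start at discharge or 5 days after randomisation, and nothing in the article suggests that their allocation alters the speed of the initial transfusion.
- **That the sepsis and malaria subgroups share the fault.** Sample timing for these is commonly left to the analysis plan, and the article fixes nothing wrong on it.

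**Conclusion.** The point holds for R1. Listing transfusion speed as an a priori effect modifier treats a post-randomisation variable as if it were a patient characteristic, and the resulting R1 interaction test could not be interpreted. This conclusion needs no assumption beyond the order of events that the article describes.

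The size of the imbalance does depend on assumptions. With one product and ml/kg/h at nominal volumes, the arms separate completely (whole blood) or meet at one value (packed cells). With products pooled and durations uniform within the windows, the fast half holds 79–93 % of the liberal arm and 7–21 % of the conservative arm over packed-cell shares of 10–75 %. With speed in hours, the windows create no imbalance. For transfusion versus no transfusion in R1b, the interaction cannot be estimated under any definition.

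The consequence is confined to one secondary subgroup analysis. The primary analysis, the alpha of 0.013, the sample size and the R2 and R3 comparisons are not affected.

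**What to change.** Remove transfusion speed from the a priori subgroup list for R1. Report delivered volume, duration and rate by arm and by blood product as a description of how the strategies were carried out. If a relation between rate and outcome is still of interest, analyse it within arm, in transfused children only, and label it observational, so that it is not presented as a test of a randomised effect.

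The cost is one list item and a sentence of relabelling. No extra data, no change in sample size and no change in patient care are involved.

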#### R2 micronutrient support

Simultaneously to R1 randomisations, all children entering the trial will also be randomly allocated on a 1:1 basis to receive either multi-vitamin multi-mineral mix (MVMM: Nutromix™ which contains iron, folate and other MVMM) or iron and folate alone (at WHO-recommended doses) for 3 months post discharge. Nutromix™ has been specifically designed for children of 6–24 months of age with SA [34–36]. The formulation, meets the recommended nutrient intake (RNI), particularly for vulnerable groups during emergencies [37]. RNI is defined as the daily dietary intake of a nutrient sufficient to meet the nutrient requirements of nearly all apparently healthy individuals in a specific population group, usually by age and sex. The dosage is 1 sachet to be taken daily by the child [26] and will be prescribed at the time of discharge from hospital (or 5 days from randomisation in those not discharged by this timepoint). In those children receiving iron (syrup or tablets) and folate tablets, for children aged < 2 years the recommended dosages are 25 mg iron: 100–400 μg folate; and for children > 2 years and < 12 years, 60 mg iron: 400 μg folate. Iron, folate and MVMM will all be given for 3 months, according to WHO guidelines for the management of SA.

The use of nutritional supplementation, including MVMM randomisation, will be pragmatic in that all children for whom these supplements should be received, according to WHO or national guidelines (e.g. those initially admitted with severe malnutrition), will receive them. Children aged < 6 months who are not weaned (fully breast-fed) will be excluded from the trial. For children with severe malnutrition, iron-containing supplements are not recommended during the first 7 days of acute rehabilitation (WHO guidelines) [3] but can be used effectively after this. For children with severe malnutrition discharged on ready-to-use therapeutic food (RUTF) which contains MVMM, children will essentially ignore their allocated MVMM randomisation, but will receive their standard post-discharge supplementation within the RUTF which would be recorded on study CRFs. The number of children with severe malnutrition as their admission diagnosis is expected to be small (< 5 %).

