#### R3 antimicrobial prophylaxis

Children will be randomly allocated on a 1:1 basis to receive either receive: (i) cotrimoxazole prophylaxis for 3 months post discharge or (ii) no antibiotic prophylaxis post discharge (control, SOC). Cotrimoxazole dispersible tablets (240 mg: trimethoprim 40 mg/sulphamethoxazole 200 mg) will be used and dosing will follow WHO recommendations for prophylaxis in HIV-infected children: age 2 to 6 months: 120 mg; age 6 months to 5 years: 240 mg; children > 5 years: 480 mg [38]. The dispersible tablets may be taken with water or mixed with feeds. Cotrimoxazole will be prescribed from discharge (or 5 days from randomisation in those not discharged by this timepoint). The cotrimoxazole prophylaxis randomisation will be pragmatic in that all children for whom cotrimoxazole prophylaxis should be prescribed according to WHO or national guidelines (e.g. HIV-infected children) will receive it regardless of randomisation, and no child in whom it is contraindicated (e.g. known GP6D deficiency according to local testing) will receive it. Such children will essentially ignore their allocated cotrimoxazole randomisation; any cotrimoxazole received per guidelines would be recorded on study CRFs. The number of children with these conditions is expected to be small (< 5 %). HIV-infected children will receive antiretrovirals and will continue in the trial with HIV management and follow-up tailored in collaboration with local HIV clinics.

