### Sample size calculation and statistical analysis

#### Sample size

The sample size calculation is based on the following assumptions:80 % power, 2-sided alpha = 0.013 to allow for 4 comparisons (see below)SA cases are 50 % complicated (< 4 g/dl or 4–6 g/dl with prostration/respiratory distress/known sickle cell disease/haemoglobinuria) and 50 % uncomplicated (4–6 g/dl without prostration, respiratory distress, known sickle cell disease or haemoglobinuria) [12] (and [name] personal communication)Mortality (cumulative) at 48 hours and 4 weeks is 11 % and 16 % respectively in complicated SA, and 4 % and 9 % in uncomplicated SAThe cumulative rate of re-admission, SA relapse and re-transfusion at 6 months is 12.5 % in both complicated and uncomplicated SA (in addition to mortality above)For the primary comparison of transfusion versus no transfusion in uncomplicated SA at 4 weeks, the minimum clinically relevant difference is a 50 % relative reduction (R1b): for the other primary comparison of transfusion volume (20 versus 30 ml/kg) at 4 weeks (R1a and 1b), the minimum clinically relevant difference is a 30 % relative reduction. The minimum clinically relevant difference is larger for the transfusion versus no transfusion question as provision of safe blood at all will require greater resources than provision of slightly larger versus slightly smaller blood volumes. As the same relative difference translates to a far larger absolute difference at higher event rates, for the primary comparison at 6 months (R2/3) the minimum clinically relevant difference is a 5 % absolute reduction (see below for control group event rates). Then:(R1b) comparison of transfusion versus no transfusion (50 % reduction from 9 % control mortality at 4 weeks) requires 1460 uncomplicated SA cases (1:1 allocation to 30/20 ml/kg:no transfusion, 730 in no transfusion group, 365 receiving 20 ml/kg and 365 receiving 30 ml/kg transfusions)(R1a and 1b) if the overall ratio of uncomplicated:complicated SAs is 1:1 (ie 50 % of each type), then within the subgroup randomised 1:1 to 30 versus 20 ml/kg, the ratio will be 1:2 because this comparison excludes the 50 % of uncomplicated SA randomised to no transfusion. Overall mortality at 4 weeks in this group will, therefore, be 13.67 % (0.33 × 9 % + 0.67 × 16 %). The comparison of 30 versus 20 ml/kg (30 % reduction, to 9.57 %) requires 2798 SAs, 1399 per group (split 466 uncomplicated, 933 complicated)Therefore, comparing required sample sizes for R1a and R1b, to address both parts of the transfusion question (R1) we need slightly more uncomplicated SA children per group from (R1a and 1b – *n* = 466) than (R1b – *n* = 365), and therefore the total sample size is 3730 cases (933 × 2 = 1866 complicated, 466 × 4 = 1864 uncomplicated)(R2/3) the comparison of multi-vitamins versus SOC (1:1) and cotrimoxazole prophylaxis versus SOC (1:1) requires 3162 SA cases, assuming 50 % are complicated and 50 % uncomplicated, to detect a 5 % absolute reduction from average control mortality of 25 % (0.5 × 21.5 % + 0.5 × 28.5 % at 4 weeks).

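### The two secondary R2/R3 analysis sets require discharge alive, which for children started on day 5 in hospital comes after treatment has begun

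*Protocol article*

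**What the plan says.** R2 and R3 are allocated at enrolment together with R1, from one card in the clinical pack (Randomisation procedures; R2 micronutrient support). Treatment comes later. Under R3 antimicrobial prophylaxis: "Cotrimoxazole will be prescribed from discharge (or 5 days from randomisation in those not discharged by this timepoint"). Under R2 micronutrient support, the supplement "will be prescribed at the time of discharge from hospital (or 5 days from randomisation in those not discharged by this timepoint"). Each child thus has one start point, the earlier of discharge and day 5.

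For both randomisations the Statistical analysis section states that "the primary analysis will be intention-to-treat based on all randomised participants, as above". It then adds that "secondary analyses will be restricted to: (i) patients discharged alive". Set (ii) keeps the discharged-alive condition and also removes children for whom the intervention was mandated or contraindicated. Neither set is defined by the start point.

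**The concern.** The restricted sets are evidently meant to show the effect in children who could receive the interventions. For a child discharged by day 5 the definition works, because discharge and start coincide. For a child still in hospital on day 5, treatment begins then and discharge alive is a later event. Requiring it selects on something treatment may change.

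If the intervention prevents in-hospital deaths after day 5, those prevented deaths cannot count in its favour. The treated arm also retains sicker survivors, whose counterparts in the control arm died and were removed, so the benefit is understated. If the intervention causes such deaths, the harm is hidden. Children still in hospital on day 5 are plausibly among the sickest, so the deaths removed need not resemble those that remain. Readers will turn to these two sets to judge the effect in children who actually started, so the loss matters although the sets are secondary.

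**Working it through.** **1. Which deaths each set counts.** I take prescribing as the start of treatment.

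| Course of the child | Treatment started before death? | All randomised | Sets (i) and (ii) as written | Alive at earlier of discharge and day 5 |
|---|---|---|---|---|
| Dies in hospital before day 5 | No | Counted | Excluded | Excluded |
| Discharged by day 5, dies later | Yes | Counted | Counted | Counted |
| In hospital on day 5, starts, dies in hospital | Yes | Counted | **Excluded** | Counted |
| In hospital on day 5, starts, discharged, dies later | Yes | Counted | Counted | Counted |

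(Set (ii) and its revised counterpart also apply the mandated/contraindicated exclusions.) The definitions differ only in the third row, which holds deaths after the start of treatment.

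**2. Upper bound on the third row, to 4 weeks.** Inputs from the Sample size section: cumulative mortality at 48 hours and 4 weeks is 11% and 16% in complicated severe anaemia, and 4% and 9% in uncomplicated; the case mix is 50:50; the total is 3730, raised to 3954 for loss to follow-up.

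- By 48 hours: 0.5 × 11% + 0.5 × 4% = 7.5%.
- By 4 weeks: 0.5 × 16% + 0.5 × 9% = 12.5%.
- Between the two: 12.5% − 7.5% = 5%. Each stratum also gives 5% (16 − 11 and 9 − 4), so the figure does not depend on the case mix.
- In numbers: 0.05 × 3730 = 186.5, about 187 children; 0.05 × 3954 = 197.7, about 198.

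**3. Why this is a ceiling.** The 5% also contains deaths in hospital between 48 hours and day 5, which precede treatment, and deaths after discharge, which sets (i) and (ii) keep. Only in-hospital deaths after day 5 are lost, and the documents give no split. Purely as an assumption: if a quarter of the 5% were such deaths, the sets would drop 0.25 × 186.5 ≈ 47 children of 3730; if half, 0.5 × 186.5 ≈ 93. In-hospital deaths after 4 weeks would come on top, and the documents give no figure for them.

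**4. Bias.** Its size depends on how many third-row deaths occur in each arm. Nothing in the documents allows that to be calculated, so only the mechanism and the ceiling can be stated.

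**The case against.** The affected analyses are secondary, the article describes the interventions as post-discharge, and it defers detail to a full analysis plan. On that view, discharged alive simply follows the question as framed. It stands that only secondary analyses are touched and that no material bias has been shown. But the restriction is stated in the article, not left open, and it does not fit the article's own day-5 start rule. An analysis plan that followed it would carry the problem forward.

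A second objection is that a set defined at the start of treatment is also not all randomised. Allocation is open from admission, and the timing of an early discharge is a clinical decision made with allocation known. That stands, and it is why the redefined set should remain secondary. Discharged alive has the same weakness and adds selection after treatment has begun.

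A reader might go further and infer that the all-randomised primary set is itself wrong, because it counts early deaths that neither intervention could have prevented. The documents do not support that. Intention-to-treat from randomisation is valid; such deaths dilute a difference but do not bias the comparison, and the restricted sets appear to be the plan's own answer to the dilution. Nor does the sizing show a shortfall against its target. The section specifies "80 % power, 2-sided alpha = 0.013 to allow for 4 comparisons" and a design "to detect a 5 % absolute reduction from average control mortality of 25" per cent. The continuity-corrected formula for 25% versus 20% gives 1581 per arm, 2 × 1581 = 3162, as the plan states: "cotrimoxazole prophylaxis versus SOC (1:1) requires 3162 SA cases". At 3730 the same formula gives about 87% power. The 25% cannot measure dilution in the mortality endpoint either: it adds readmission, relapse and re-transfusion at a rate that "is 12.5 % in both complicated and uncomplicated SA (in addition to mortality above"), whereas the R2/R3 primary outcome in Table 3 is mortality to 180 days.

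**Conclusion.** The point holds for the two secondary sets only. For children started on day 5 in hospital, sets (i) and (ii) condition on an event after the start of treatment and leave out in-hospital deaths on treatment. The direction is towards hiding an effect, whether benefit or harm, on those deaths. Up to 4 weeks the number dropped is at most 5% of children (about 187 of 3730), on the plan's own mortality assumptions and with prescribing taken as the start; the actual number cannot be derived from the documents. The primary intention-to-treat analysis is unaffected, and there is no case here for replacing it with a post-randomisation subset in an open trial. The correction is worth making because it is specific, nearly free, and bears on the analyses closest to the effect in children who started treatment.

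**What to change.** Keep intention-to-treat in all randomised children as the primary R2/R3 analysis. In sets (i) and (ii), replace the discharged-alive condition with: alive and in the trial at the earlier of discharge and day 5 after randomisation. Count follow-up time from that point. Leave the mandated/contraindicated exclusions in (ii) as they are. Tabulate deaths before that point by R2 and R3 arm, so that readers can see whether the arms were balanced when treatment became available.

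The cost is one definition and one table. It should need no new data collection, since survival status and hospital stay are already recorded, and no change to treatment. The limitation to state alongside the results is that the set is still not all randomised and allocation is open, so it supports the primary analysis and does not replace it.
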